### 2.4. Randomization and allocation

Patients are randomized into three groups using a random number table, with allocation via sequentially numbered, opaque, sealed envelopes. Upon determining the eligibility of the subjects, the envelopes are opened in sequence and the subjects are assigned to the corresponding test group.

The researcher generating and preserving the random sequences is separated from the trial and will have no clinical involvement. Neither the subjects nor their routine care therapists will be aware of the group assignments.

### 2.5. Interventions

The trial’s structure and implementation process are depicted in Figure 2. The RStDCS group undergoes upper limb rehabilitation training, complemented with reward strategies and non-invasive neuromodulation techniques. This aims to stimulate patients’ intrinsic motivation through tDCS stimulation of the left dorsolateral prefrontal cortex (dlPFC), an area implicated in predicting successful effort extension. This enables the dorsal anterior cingulate cortex (dACC) to balance potential benefits against required work (46). All the electrodes are placed in saline soaked sponge (5 × 7 cm^2^). The anodal electrode is positioned over left dlPFC (between F3 and F7) according to the International 10–20 system, with cathodal electrode contralaterally on right shoulders. Anodal stimulation is administered at a continuous current of 1.5 mA (0.043 mA/cm^2^ current density over 35 cm^2^ electrodes) for 20 min daily over 3 weeks, totaling 15 sessions. The tDCS stimulation consisted of fade-in and fade-out periods of 30 s to minimize discomfort.

**Figure 2 fig2:**
[figure not shown]
Groups overview and research implementation process.

In contrast, the RS group undergoes upper extremity rehabilitation with reward strategies and sham tDCS stimulation, identical in position to the RStDCS group. The current is ramped up and then immediately ramped down in the sham condition in 60 s to mimic the perception of current onset.

Reward strategies involve offering extrinsic rewards in recognition of patients’ independent performance encouraging sustained active rehabilitation motivation. Specifically, a 21-day inpatient-training manual is developed for chronic stroke patient with upper limbs dysfunction and low motivation. Upon discharge, a 21-day home training program is customized for each patient. Figure 3 shows the schematic diagram of reward strategy self-monitor brochure in in-patient and out-patient settings. Both program are tailored according to the Brunnstrom stage of upper limbs and hands, passive range of motion (PROM), muscle tone, muscle strength, fine motor abilities, grip strength, and activities of daily living (ADL). They incorporate exercises to improve and maintain joint mobility, therapeutic exercises, functional training, and ADL training. The Supplementary File 3 shows the contents of the library of active exercise program.

**Figure 3 fig3:**
[figure not shown]
Schematic diagram of reward strategy self-monitor brochure in in-patient and out-patient settings.

During their 21-day hospital stay, patients in the RStDCS and RS groups undertake the program following their 20-min tDCS stimulation; patients implement the program through self-report and free choice. Therapists award points based on daily task completion. At home without supervision, patients select their task training and self-record their progress to foster intrinsic motivation. At the program’s conclusion, points are tailed and redeemable for gifts (maximum available points can be 2,142, which can exchange gifts worth 267 RMB).

The control group receives conventional upper limb rehabilitation training and sham tDCS stimulation without rewarding strategies. They undergo 20-min training sessions, 5 days a week for 3 weeks. Post-discharge rehabilitation education is provided.

### 2.6. Outcomes measures

Patients are evaluated at baseline, 3 and 6 weeks and at a 3-month follow-up using assessment scales and behavioral observations. Basic data (gender, age, disease duration, affected side, etc.) are extracted from electronic medical records. All data are entered into the paper Case Report Form (CRF) and uploaded to a protected research server online. The assessors are trained prior to data collection. Assessment scales include Rehabilitation Motivation Scale (RMS), Fugl-Meyer Assessment Scale (FMA), Function Independent Measure (FIM), ICF Activity, and Participation Scale (ICF).

#### 2.6.1. Primary outcome measures

The RMS, designed by Litman in 1961 to observe the motivation of patients to participate in physical therapy. Later, it was adapted into a Chinese version by [name] team. This examiner-rating scale has demonstrated a significant interrater reliability of 0.648 (*p* < 0.001) (22). The content includes complaining level, cooperation level, avoidance, seeking encouragement, pain complaining level, seeking resources, effort level, and attitude on rehabilitation. There are eight questions in total, which are scored by Likert four-point scoring method. Q1, Q4, Q6, and Q8 are positive questions, Q2, Q3, Q5, and Q7 are negative questions, and the score of negative questions are calculated by five minus chosen points. The minimum score of this scale is 8 and the maximum is 32. A score of more than 25 is considered as high motivation. The content of the evaluation scale is in the Supplementary File 1.

#### 2.6.2. Secondary outcome measures

The FMA, created by Swedish doctor Fugl-Meyer on the basis of Brunnstrom rating Scale in 1980. It is a widely recognized and frequently used, with proven reliability and validity (47). FMA can help to monitor and measure the level of ICF structure and function in patients. The FIM, proposed by researchers from the Functional Assessment Research Center of New York State in 1987, assesses the ADL ability of stroke patients comprehensively and objectively (48). The ICF Activity and Participation Scale appraises the health status and health-related condition over the past 30 days covering six areas: understanding and communication, physical activity, self-care, interpersonal interactions, life activity, and social participation. Both FIM and ICF Activity and Participation can measure the level of ICF Activity and Participation level.

Behavioral observation data included the number of therapist-supervised active exercise sessions during hospitalization and the number of self-reported active exercise sessions by patients at home. After 42 days of reward training, the researchers collect the program manual and tally the number of completed sessions.

### 2.7. Data management

Data from patients are gathered using CRFs that comply with the Good Clinical Practice (GCP) standards. Researchers store the assessment results on a protected research server and routinely back up the research folders every 3 months. Informed consent and CRF paper forms are stored in a locked room in the institute’s office. All paper raw data and analysis procedures will be archived to enable future researchers to reproduce or reuse the experimental data.

In data storage, patient study results are recorded using a serial number as a marker. The key to the serial numbers is held by the principal investigator. Only authorized researchers can access this key during the study period, and no participant information will be made public.

### 2.8. Statistics

#### 2.8.1. Sample size

Sample size estimation was made assuming a medium effect size (0.25) seen in previous similar studies (49, 50). G*power software (3.1.9) is used with the means of ANOVA Repeated measures, within-between interaction. The type of power analysis is *a priori*: compute required sample size-given α, power, and effect size. The calculation indicated a sample size of 72 subjects with a desired power of 0.90 at a 5% significance (two-tailed), correlation coefficient of 0.5, and nonsphericity correction of 0.5. Factoring in a 15% dropout rate, we estimated that each group should comprise 29 subjects, making a total of 87 subjects across the three groups.

#### 2.8.2. Statistical analyses

SPSS 26.0 version will be used for data analysis. Chi-square tests are used to compare count data, and descriptive statistical analyses is conducted to study the basic information of subjects in RStDCS group, RS group, and control group. Independent sample *t* tests will be used for intergroup comparisons of measurement data following a normal distribution, while paired sample *t* tests will be used for intragroup comparisons, represented as “(
$\bar{x}$
±s).” If the data do not follow a normal distribution, independent sample rank sum tests will be used for intergroup comparisons, and paired sample rank sum tests for intragroup comparisons, represented as [M (P25, P75)]. To investigate the impact of using reward strategies combined with neuromodulation techniques on upper limb dysfunction in chronic stroke survivors with low motivation over time, a repeated measure ANOVA will be performed, with rehabilitation motivation, motor function, functional independence, ICF activity, and participation as dependent variables. The model includes three groups (RStDCS group, RS group, and control group) and three test types (0, 3, and 6 weeks). Due to the strict requirements for repeated measurement data, missing cannot occur. If a sample lacks measurement data, all the data from that sample will be excluded from the model during analysis. A value of *p* less than 0.05, two-tailed, is considered statistically significant.

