**Methods and design:**

Eighty-seven stroke survivors with low motivation and upper extremity dysfunction will be randomized to receive either conventional treatment, RS treatment, or RStDCS treatment. The RStDCS group will receive reward strategies combined with anodal tDCS stimulation of the left dlPFC. The RS group will receive reward strategies combined with sham stimulation. The conventional group will receive conventional treatment combined with sham stimulation. tDCS stimulation is performed over 3 weeks of hospitalization, 20 min/time, five times a week. Reward strategies refers to personalized active exercise programs for patients during hospitalization and at home. Patients can voluntarily choose tasks for active exercise and self-report to the therapist so as to punch a card for points and exchange gifts. The conventional group will receive home rehabilitation instructions prior to discharge. Rehabilitation motivation, measured using RMS. RMS, FMA, FIM, and ICF activity and social engagement scale will be compared at baseline, 3 weeks, 6 weeks, and 3 months post-enrollment to evaluate patients’ multifaceted health condition based on the ICF framework.

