### 1.1. Objectives

This randomized controlled trial intends to evaluate the effectiveness of reward strategies combined with tDCS (RStDCS) in improving rehabilitation motivation in 87 patients with chronic stroke (onset over 6 months), compared to RS group without tDCS and conventional treatment group. Through this pilot study, we aim to verify whether reward strategies designed to boost rehabilitation motivation can provide a feasible approach throughout the entire “hospital, home and society” rehabilitation process. The primary objective is to compare the scores of rehabilitation motivation scale and the frequency of patients participating in unsupervised exercises at baseline, 3 weeks, 6 weeks after treatment, and at a 3-month follow-up. The secondary objective is to evaluate the structure and function, activities, and participation of patients within the framework of ICF to observe whether reward strategies can improve rehabilitation motivation, motor ability, daily living ability, and quality of life through self-reporting and assessment instruments.

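### Two-group t or rank-sum tests at 0.05 in a three-arm trial, not tied to the planned repeated-measures ANOVA, inflate the false-positive risk on the motivation scale

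*Protocol article*

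**What the plan says.** Section 2.8.2 of the protocol article describes two layers of between-group analysis.

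- **Two-group tests.** Independent-sample t "tests will be used for intergroup comparisons of measurement data following a normal distribution". If normality fails, "independent sample rank sum tests will be used for intergroup comparisons".
- **Repeated-measures ANOVA.** It is run "with rehabilitation motivation, motor function, functional independence, ICF activity, and participation as dependent variables". Its scope is given as "The model includes three groups (RStDCS group, RS group, and control group) and three test types (0, 3, and 6 weeks".

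One criterion closes the section: a p value "less than 0.05, two-tailed, is considered statistically significant". No sentence says that the two-group tests follow only from a significant ANOVA, or which of the two layers decides the trial.

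Section 1.1 sets the aim as effectiveness of the combined treatment (RStDCS) "compared to RS group without tDCS and conventional treatment group". The main goal is put there in these words: "compare the scores of rehabilitation motivation scale and the frequency of patients participating in unsupervised exercises at baseline, 3 weeks, 6 weeks after treatment". A 3-month assessment completes that list of visits. The abstract says the scales "will be compared at baseline, 3 weeks, 6 weeks, and 3 months post-enrollment". Section 2.6.1 makes RMS the primary measure. Section 2.6.2 lists FMA, FIM and the ICF scale as secondary.

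**The concern.** An independent-sample t test compares two groups. With three arms it has to be run up to three times per scale and visit, and the stated rule judges each run at 0.05. A three-group test could contain this, but the plan does not link its ANOVA to the pairwise tests. The ANOVA also stops at 6 weeks. At 3 months, the two-group tests are the only between-group method that section 2.8.2 offers for scale scores.

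What is at stake is the meaning of a positive result. If the ANOVA interaction is not significant but one pairwise test at one visit is, the text does not say which prevails. A claim resting on the pairwise test would carry an error rate well above the stated 5%.

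**Working it through.** **1. Which test the trial is sized on.** Section 2.8.1 gives effect size f = 0.25, correlation 0.5, nonsphericity correction 0.5, power 0.90 and 5% significance, for the within-between interaction. Section 2.8.2 gives three groups and three time points.

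- Noncentrality = f² × N × m × ε / (1 − ρ) = 0.0625 × 72 × 3 × 0.5 / 0.5 = 13.5.
- df1 = (3 − 1)(3 − 1)(0.5) = 2; df2 = (72 − 3)(3 − 1)(0.5) = 69.
- Power at N = 72 is 0.906, and 72 is the smallest multiple of 3 that reaches 0.90. Four time points would give 60.
- Dropout: 24 / (1 − 0.15) = 28.2, rounded up to 29 per group; 3 × 29 = 87.

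The stated 72 and 87 reproduce. The sample size belongs to the group-by-time test at 0, 3 and 6 weeks, not to the two-group tests.

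**2. What the two-group tests do if used as stated on RMS.** Three arms give 3 pairs. Three independent tests would give 1 − 0.95³ = 14.3%, and nine would give 1 − 0.95⁹ = 37.0%. Pairs share arms and visits share patients, so the true figures are lower. They were obtained by simulation with normal data, no true difference, 24 or 29 per arm, two-sided t tests at 0.05 and at least 20,000 trials per setting. Baseline is not counted.

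| RMS visits tested | Pairs counted | Visit correlation | Chance of at least one p < 0.05 |
|---|---|---|---|
| One | all 3 | not applicable | about 12% |
| One | RStDCS against each comparator | not applicable | about 9% |
| Weeks 3 and 6 | all 3 | 0.5 | about 21-22% |
| Weeks 3 and 6 | all 3 | 0.8 | about 18-19% |
| Weeks 3, 6 and 3 months | all 3 | 0.5 | about 29% |
| Weeks 3, 6 and 3 months | all 3 | 0.8 | about 23% |
| Weeks 3, 6 and 3 months | RStDCS against each comparator | 0.5 | about 22% |

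The correlation of 0.5 is the protocol's own planning value; 0.8 is an assumption to show sensitivity. Over correlations from 0.9 to 0, the three-visit figure for all pairs runs from 19% to 32%. The rank-sum version was not simulated.

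**3. Whether a gate would cure it.** At one visit, a three-arm test (2 df) at 0.05 was followed, only if significant, by the three pairwise contrasts at 0.05 each. The familywise error was 5.2% with no true difference and 4.7% with one arm truly different. Both are 5% within simulation error. With exactly three arms this is a closed procedure: once one arm truly differs, at most one true null contrast is left to reject.

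**The case against.** The strongest reply is that the ANOVA is the real analysis. It is a three-group test on RMS, it is introduced as the way to study the intervention's impact over time, and the sample size rests on it. On that reading the t tests are descriptive or follow-up, and the 12-29% does not arise. This stands in part. It would be wrong to infer that the plan has no overall test. But the text lists the two-group tests separately, under the same 0.05 rule, with no condition attached, and the ANOVA does not reach 3 months.

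Some further points limit the size:

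- **Visits.** Section 2.8.2 lists no visits for the two-group tests. They are inferred from the abstract and section 1.1. If only the ANOVA's post-baseline visits count, the ceiling is about 21-22% at correlation 0.5.
- **Decision rule.** A reader might infer that any one of nine RMS tests (3 pairs × 3 visits) would count as proof of effectiveness. The protocol does not say so. The section 1.1 effectiveness claim concerns RStDCS, which RS against control cannot support. If superiority to both comparators were required at one given visit, the error would not exceed 5%.
- **Other scales.** Counting 3 pairs × 3 visits × 4 scales = 36 tests is tempting, but three of the four scales are secondary and do not bear on the primary claim.
- **Rank-sum wording.** It does not exclude a rank test for several groups.
- **Unseen plan and pilot status.** Multiplicity detail is commonly left to an analysis plan, so its absence here is no finding. The trial also calls itself a pilot. Yet it sets out to evaluate effectiveness with 90% power at 5%, and the point concerns a rule that is stated.

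**Conclusion.** The point holds as a defect in a stated rule: two-group tests at 0.05 in a three-arm trial, not tied to the three-group model. Used as written on RMS, they give a false-positive chance of about 12% at one visit (9% for the two RStDCS contrasts), about 21-22% over weeks 3 and 6 at correlation 0.5, and about 23-29% with 3 months added (correlation 0.8 to 0.5).

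These figures assume that no group truly differs, that the ANOVA does not act as a gate, that the tests are run at the inferred visits, and that any significant result among the counted tests is read as positive. The documents do not support saying that the trial's primary claim will certainly carry a 29% error rate, because the ANOVA may be the intended deciding test. What they show is that the text does not say so, and that every counting of unlinked pairwise tests in the table exceeds 5%.

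**What to change.** Revise section 2.8.2, and carry the change into any analysis plan, before outcome data are seen by group:

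1. Name the group-by-time test for RMS in the repeated-measures model as the single primary test at 0.05. The sample size already rests on it.
2. Remove the stand-alone t and rank-sum tests as between-group tests of the outcomes. Replace them with pairwise contrasts of change from baseline, taken from that model, at one visit named in advance.
3. Test those contrasts at 0.05 each only if the primary test, and then the three-arm (2-df) test at the named visit, are both significant. Alternatively, use Holm-adjusted contrasts: the smallest p against 0.05/3 = 0.0167, the next against 0.025, the last against 0.05.
4. Report other visits, including 3 months unless it is added to the model, and FMA, FIM and the ICF scale as secondary, with confidence intervals.

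The cost is wording: no extra patients, visits or data. Fewer results can be called confirmatory, and power for individual pairwise contrasts is slightly lower. Making 3 months the primary visit would be a larger step. It lies outside the stated model and changes the hypothesis that the 72 patients were calculated for, so power would need a fresh check.

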## 2. Methods and analysis

### 2.1. Study design

The reward strategy combined with tDCS treatment (RStDCS) for improvement of rehabilitation motivation after stroke study is a randomized, single blind, controlled clinical trial. Subjects will be randomly assigned to either the RStDCS group, the reward strategy with sham tDCS treatment group (RS group), or the conventional treatment with sham tDCS treatment (Control group). All patients will receive either true or sham tDCS stimulation and will be provided with an exercise program manual (content varies based on different requirements). Evaluators and statisticians will remain blind to the subjects’ group assignments. Assessments will be conducted at 0, 3, and 6 weeks and followed up at 3 months using assessment scales and behavioral observations. Prior to the assessment, the evaluator will be trained. Assessment scales include the Rehabilitation Motivation Scale (RMS), Fugl-Meyer Assessment Scale (FMA), Function Independent Measure (FIM), and ICF Activity and Participation Scale (ICF). Table 1 shows the schedule of enrollment, interventions, and assessments.

**Table 1 tab1:** The schedule of enrolment, interventions, and assessments.

	Study period				
	Enrolment	Allocation	Post-allocation		Close-out
Timepoint**	*−1 day*	0 day	*3 weeks*	*6 weeks*	*3 months*
Enrolment:					
Eligibility screen	X				
Informed consent	X				
Allocation		X			
Interventions:					
Group A (RStDCS)					
Group B (RS + sham)					
Group C (Conventional + sham)					
Assessments:					
RMS		X	X	X	X
FMAS		X	X	X	X
FIM		X	X	X	X
ICF		X	X	X	X

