### 2.3. Inclusion and exclusion criteria

Eligible patients should meet the following criteria:

Able to provide written informed consent and understand study’s content, follow-up requirements and are willing to complete questionnaires and provide the necessary information at follow-up visits.Diagnosed with stroke based on the diagnostic criteria for ischemic stroke set by the National Cerebrovascular Academic Conference in 2014.Age 18–70 years, no gender limitation, right-handed.No cognitive impairment or communication impairment, Mini-Mental State Test (MMSE) score of ≥ 27 (43).First stroke onset with the course of disease lasting more than 6 months，less than 3 years.Upper limb and hand dysfunction, Brunnstrom Stage ranged from I to VI.Patients’ rehabilitation motivation scale score of ≤25.

The exclusion criteria of this study are:

Serious systemic diseases such as cardiopulmonary diseases that would prevent them from tolerating rehabilitation treatment.(History of) Psychosis, major depression (including suicidal tendencies) or epilepsy, HAMD−17 scores>24 (44).Presence of severe systemic diseases such as diabetes and uremia.Severe joint contracture.Any form of consciousness disturbance (somnolence, confusion, stupor, coma, and delirium, etc.) due to any cause, Glasgow coma score < 15 (45).Contraindications for tDCS according to safety guidelines, such as implanted metal foreign bodies or other electronic devices.Auditory or visual impairment may affect assessment and treatment.Use of drugs that alter the excitability of the cerebral cortex (like antiepileptic drugs, sedatives, and hypnotics, etc.).Severe pain, sleep disturbance, or mental disorder.

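### Within-arm paired tests are not evidence of efficacy, and the pairwise and 3-month arm comparisons rest on tests that make no use of baseline

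*Protocol article*

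**What the plan says.** Section 2.8.2 sets out three kinds of analysis.

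- Between arms: independent-sample t "tests will be used for intergroup comparisons of measurement data following a normal distribution", with rank-sum tests otherwise. No baseline term or change score is named.
- Within arms: paired-sample t "tests will be used for intragroup comparisons", with paired rank-sum tests otherwise.
- Over time: "a repeated measure ANOVA will be performed, with rehabilitation motivation, motor function, functional independence, ICF activity, and participation as dependent variables". The model has the three arms and "three test types (0, 3, and 6 weeks", so baseline is one of the repeated outcomes.

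One two-tailed threshold of 0.05 applies to all of these.

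Section 1.1 gives the objective as RStDCS compared with RS and with conventional treatment, and includes the 3-month follow-up. Section 2.1 agrees on the visits: "Assessments will be conducted at 0, 3, and 6 weeks and followed up at 3 months".

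On RMS, the primary outcome, Section 2.3 requires a "rehabilitation motivation scale score of ≤25". Section 2.6.1 reports a "significant interrater reliability of 0.648" and states: "The minimum score of this scale is 8 and the maximum is 32". Table 1 marks RMS at day 0 and shows no RMS at the eligibility screen one day earlier. Section 2.2, however, puts at least two weeks between being found eligible and signing consent.

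**The concern.** There are two separate problems.

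**Between arms.** The ANOVA interaction is an omnibus test over three arms and ends at week 6. It does not say whether RStDCS beats RS or beats control, and it says nothing about 3 months. The only stated tests that can answer those questions are the t or rank-sum tests, which do not use a baseline that is collected on all four scales. With about 24 to 29 patients per arm, this wastes precision and leaves chance baseline imbalance in the estimate.

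**Within arms.** A paired test mixes any treatment effect with natural course, attention, repeat rating and regression to the mean. A significant result in one arm beside a non-significant one in another does not test the difference between them. RMS has the added problem that patients enter because their score is low, on an imperfectly reliable scale. If that same score is the baseline, the expected change is upward with no treatment effect at all.

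**Working it through.** **1. The plan's own figure.** Section 2.8.1 gives f = 0.25, correlation ρ = 0.5, nonsphericity correction ε = 0.5, power 0.90 and α = 0.05. With k = 3 arms and m = 3 times:
- λ = f²·N·m·ε/(1−ρ) = 0.0625 × 72 × 3 × 0.5/0.5 = 13.5
- df1 = (k−1)(m−1)ε = 2; df2 = (N−k)(m−1)ε = 69
- Power = 0.906, and 72 is the smallest total in equal arms that reaches 0.90.
- Dropout: 24/0.85 = 28.2, so 29 per arm and 87 in all.

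The figure reproduces with three time points (with four it would be 60). The trial is therefore sized on the week 0, 3 and 6 interaction, not on a pairwise or 3-month comparison.

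**2. Precision between two arms.** Variance relative to a test of the visit score alone, at ρ = 0.5:
- visit score: 1
- change from baseline: 2(1−ρ) = 1.0
- baseline as covariate: 1−ρ² = 0.75

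The article does not say whether the t tests use visit scores or change scores. At ρ = 0.5 the two have the same variance. Covariate adjustment is worth 1/0.75 = 1.33, a third more patients.

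Power for 24 per arm uses noncentrality d·√(24/2)/√v on 46 degrees of freedom; the one degree that the covariate costs is ignored. The values of d are assumptions.

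| Assumed d | Unadjusted (v = 1) | Adjusted (v = 0.75) |
|---|---|---|
| 0.65 | 2.25, power 60% | 2.60, power 72% |
| 0.75 | 2.60, power 72% | 3.00, power 84% |

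**3. Expected rise in RMS with no effect.** This applies only if the qualifying score is the baseline. Assumptions: normal scores in the screened population, mean μ 22 to 26, SD 3 to 5, and repeat-rating correlation r = 0.648 (the inter-rater figure used as a proxy). The cut is at 25.5 because scores are whole numbers.

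Rise = (1−r)·SD·h, with h = φ(a)/Φ(a) and a = (25.5−μ)/SD.
- μ = 22, SD 3: a = 1.167, h = 0.230; 0.352 × 3 × 0.230 = 0.24 points
- μ = 26, SD 5: a = −0.10, h = 0.863; 0.352 × 5 × 0.863 = 1.52 points

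**4. False improvement by the paired t test, 24 per arm.** SD of change = SD·√[(1−r)²·w + 1−r²], with w = 1 − a·h − h². The nominal rate in the upward direction is 2.5%.
- μ = 22, SD 3: SD of change 2.45, noncentrality 0.49, rate about 7%
- μ = 26, SD 5: SD of change 3.95, noncentrality 1.88, rate about 44%
- μ = 26, SD 3: rise 0.96, SD of change 2.36, noncentrality 1.98, rate about 48%

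The largest rise and the largest error rate thus come from different assumed SDs. If the arms are independent, all three show false improvement in 0.066³ = 0.03% to 0.483³ = 11% of trials.

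**5. Sensitivity.** With SD 4, a cut at 25, means 22 to 28 and correlations 0.5 to 0.8, the rise runs from 0.31 to 2.66 points.

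**6. Between-arm error with no effect.** In simulation (29 per arm, mean 25, SD 4, correlation 0.648) the type I error was 0.050 for visit scores, 0.052 for change and 0.054 for ANCOVA. The entry cut does not bias the comparison between arms.

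**The case against.** Several stronger readings are tempting, and the article does not support them.

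- *Baseline is ignored throughout.* It is not. The ANOVA includes week 0, its interaction compares change between arms, and the trial is sized on it. What remains is that this model ends at week 6 and names no pairwise contrast.
- *Every arm will show a significant improvement.* A reader might infer this from the entry cut. Only the expected change is positive in every arm; significance in all three is uncommon under the assumptions above.
- *Regression to the mean biases the arm comparison.* It shifts randomised arms equally in expectation.
- *All outcomes regress.* FMA, FIM and the ICF scale have no entry cut on their own score, so this mechanism concerns RMS only.
- *The investigators will claim efficacy from within-arm tests.* The article does not say so; Section 1.1 frames effectiveness as a comparison with the other two arms.

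The strongest objection concerns timing. If eligibility is settled at least two weeks before consent, as Section 2.2 implies, the day-0 RMS may be a fresh rating. Most of the regression would then occur before baseline. Table 1 points the other way, and the two passages do not settle it. This objection stands, so the RMS rise is conditional.

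It is also fair that the two calculations use different correlations, 0.648 and 0.5. They fit together reasonably. With mean 24, SD 4 and the cut at 25.5, w = 0.453. The correlation among enrolled patients is then 0.648·√0.453/√(0.648² × 0.453 + 1 − 0.648²) = 0.436/0.878 = 0.50.

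Finally, covariate adjustment is often left to an analysis plan that is not shown. But this article does fix the tests, and the point is about the tests it fixes.

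**Conclusion.** The point holds in a limited form. The between-arm t and rank-sum tests are valid but inefficient, and as written they carry the pairwise and 3-month comparisons. The loss is 25% of residual variance at the plan's own correlation, or about 12 percentage points of power at 24 per arm for the assumed differences of 0.65 and 0.75.

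The within-arm tests are not evidence of efficacy on any scale; that conclusion needs no numerical assumption. For RMS, the extra rise of about 0.2 to 1.5 points and the 7% to 48% false improvement per arm need three things: that the qualifying score serves as baseline, that 0.648 approximates the repeat-rating correlation, and that the screened population has mean 22 to 26 and SD 3 to 5. The documents give neither that mean nor that SD. The change should be made, but the plan's between-arm inference is not invalid without it.

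**What to change.** In Section 2.8.2 or the analysis plan:

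1. Report within-arm change descriptively (mean change with its spread) and remove the paired tests as inferential analyses.
2. Base every efficacy statement on RStDCS versus RS and RStDCS versus control. Adjust each contrast for the baseline of the same scale, by ANCOVA at a visit or by a longitudinal model with weeks 3, 6 and 3 months as outcomes and baseline as covariate.
3. Include the 3-month visit explicitly in that analysis.
4. State whether the qualifying RMS is also the day-0 RMS, and reconcile Table 1 with Section 2.2 on the timing of eligibility.

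The cost is wording. All four scales are already scheduled at day 0, so no patients, visits or data are added.
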